## Abstract

**Background:**

Approximately 50% of the patients undergoing percutaneous coronary intervention (PCI) for acute coronary syndromes (ACS) have additional stenotic lesions in non-infarct-related coronary arteries. The decision whether these stenoses require further treatment is routinely based on angiography alone. The quantitative flow ratio (QFR) is a simple non-invasive method that may help quantify the functional significance of these intermediate coronary artery lesions. The aim of our single-center, randomized superiority trial is to test the impact and efficacy of QFR, as compared to angiography, in the treatment of patients with ACS with multivessel coronary artery disease. Primary goal of the study is to investigate 1. The impact of QFR on the proportion of patients receiving PCI vs. conservative therapy and 2. whether QFR improves angina pectoris and overall cardiovascular outcomes.

**Methods and Analysis:**

After treatment of the culprit lesion(s), a total of 200 consecutive ACS patients will be randomized 1:1 to angiography- vs. QFR-guided revascularization of non-culprit stenoses. Patients and clinicians responsible are blinded to the randomization group. The primary functional endpoint is defined as the proportion of patients assigned to medical treatment in the two groups. The primary clinical endpoint is a composite of death, non-fatal myocardial infarction, revascularization and significant angina at 12 months. Secondary endpoints include changes in the SAQ subgroups, and clinical events at 3- and 12-month follow-up.

**Discussion:**

This study is designed to investigate whether QFR-based decision-making is associated with a decrease in angina and an improved prognosis in patients with multivessel disease.

**Trial Registration Number:**

ClinicalTrials.gov Registry (NCT04808310).

## Introduction

Of the patients undergoing PCI for an ACS, ~50% have additional stenotic lesions in non-infarct-related coronary arteries (1). These lesions need to be correctly classified into those hemodynamically non-significant (not needing treatment) and those hemodynamically significant (needing treatment). This decision is commonly performed using angiography with visual assessment of diameter stenosis. Alternatively, a more accurate stratification can be achieved by measuring coronary hemodynamics invasively. A number of studies show that fractional flow reserve (FFR)-guided PCI is superior to angiography guided PCI in terms of mortality, infarction and unplanned revascularizations (2–4). Use of FFR and analogous indices in patients with stable coronary artery disease has been shown to improve outcomes of patients with chronic coronary syndromes (2, 3, 5–7). In the setting of ACS, three randomized trials tested the impact of an FFR-guided approach for the treatment of non–infarct-related coronary artery lesions in ST-segment elevation myocardial infarction (STEMI) patients. While DANAMI-Primulti and COMPARE Acute showed a significant reduction in repeat revascularizations in the FFR group as compared to the angiography group (8, 9), the FLOWER-MI (10) trial did not show a significant advantage with respect to the risk of death, myocardial infarction, or urgent revascularization at 1 year (10). Finally, in the FAMOUS-NSTEMI trial (11), the proportion of patients initially treated with medical therapy was higher in the FFR-guided group compared to angiography-guided group. Importantly, at 12 months, the rate of revascularization was lower in the FFR-guided group (11).

The need of additional time limit the penetration of invasive physiology assessment in clinical routine, particularly in the setting of ACS where patients need to be treated rapidly. Additionally, since they require the use of an intracoronary wire, these methods do not allow *post-hoc*, off-line measurements.

In contrast, QFR is a simple and non-invasive parameter based on three-dimensional quantitative coronary angiography (12) that allows *post-hoc*, off-line analysis without prolonging the intervention in the acute setting. A number of studies have now shown that the results of QFR correlate well with those of FFR, and a recent meta-analysis of nine studies for a total of 1,175 vessels in 1,047 patients reported a pooled sensitivity, specificity, positive and negative likelihood ratio for QFR of 0.89 (95% CI: 0.86–0.92), 0.88 (95% CI: 0.86–0.91), 6.86 (95% CI,: 5.22–9.02), 0.14 (95% CI: 0.10–0.21). The area under the summary receiver operating characteristic (sROC) curve for QFR was 0.94 (13). Further, QFR has been validated by several studies in the context of non-culprit lesions of ACS (14–18).

Recurrence of angina is a common phenomenon, which affects up to 32% of patients in the first year after PCI (19, 20). In the setting of ACS, using data from the MERLIN-TIMI 36 trial, it was shown that 4 months after ACS, ~30% of patients reported monthly angina, more than 15% weekly angina, and more than 4% daily angina (21). Our study aims to investigate whether assessment of non-culprit lesions with QFR improves outcomes of ACS patients with multivessel disease.

## Materials and Methods

### Overview

We investigate whether the use of a computerized functional assessment of stenosis severity based on 3-dimensional reconstruction of coronary anatomy using QFR improves angina pectoris and cardiovascular outcomes in patients with a successfully treated ACS and non-culprit residual intermediate coronary artery stenoses.

### Study Design

The study is a single-center, randomized, parallel, superiority trial to compare two strategies to guide revascularization of non-culprit coronary lesions in ACS patients who have undergone interventional treatment of culprit lesions. The hypothesis of the study is that QFR-guided assessment of non-culprit lesions will be associated with improved discrimination of ischemia-inducing lesions, leading to lower event rates and less angina pectoris at follow-up. The protocol complies with good clinical practice (GCP) and the ethical principles described in the Declaration of Helsinki, has been approved by the local ethics committee and registered under ClinicalTrials.gov (NCT04808310). All patients participating in the study must provide written informed consent. The study, including the initial interventional procedure, all study-related measurements and possible further procedures, will be conducted in the catheterization laboratory of the Department of Cardiology, Cardiology 1 of the University Medical Center Mainz.

### Trial Population

All patients with unstable angina, NSTEMI or STEMI who have received successful PCI (Thrombosis in Myocardial Infarction score of at least 2 and residual stenosis <30%) of all culprit lesions and receive guideline-directed medical therapy will be evaluated. Patients who present at least one non-culprit coronary artery lesion (>30 and <90% by visual estimation in a major epicardial coronary artery or major side branch measuring ≥2.0 mm in diameter) that is judged to be amenable to PCI will be screened for enrolment. Patients with multiple lesions and/or lesions in more than one vessel can be included. Patients will be excluded if any of the following criteria applies: age <18 years; persistent symptoms or evidence of ischemia (troponin raise, ST-changes, angina) following treatment of the ACS-culprit lesion and requiring (re-)intervention of the culprit or other lesions; non-culprit stenoses or patients not amenable to treatment with PCI (e.g., limited life expectancy, small-vessel disease); patients for whom PCI is believed to be an unsafe alternative (e.g., renal failure); any contraindication to PCI according to guidelines; presence of thrombus in the non-culprit lesion; participation in another randomized interventional study interfering with the present protocol; women of child-bearing potential or lactating; previous coronary artery bypass graft (CABG) surgery; recent (within 30 days) unsuccessful PCI; decompensated congestive heart failure (CHF) or hospitalization due to CHF during the last 3 months; left ventricular ejection fraction <30%; severe chronic obstructive pulmonary disease (COPD); severe valvular heart disease; FFR or RFR (resting full cycle ratio) oder iFR (instantaneous wave free ratio) assessment of non-culprit lesions at the time of the index procedure (see Table 1). Patients unable to understand the scope of the study are classified as not able to give informed consent and are ineligible for study enrollment. Likewise, patients unable to consent, e.g., for a neurological damage, are treated as not able to give informed consent and are excluded.

**Table 1 T1:**
[figure not shown]
In- and exclusion criteria.

### Study Procedures

#### Consent and Randomization

Patients will be contacted after successful interventional treatment of the ACS, which includes treatment of all culprit lesions (typically >90% diameter stenosis or thrombotic lesions) and guideline-directed medical therapy. If all inclusion and no exclusion criteria are met, consent will be obtained. Prior to randomization, QFR will be measured in all participants in all coronary arteries presenting a lesion with 30–90% diameter stenosis. Patients with vessels with residual QFR <0.80 (residual QFR is the QFR calculated in the absence of the target lesion. A QFR <0.80 assumes that treatment of this/these focal lesion(s) would not remove the source of ischemia, such as in the case of diffuse disease) will be excluded. Thereafter, randomization will be performed in a 1:1 ratio with the use of randomly permuted blocks of 2, 4 or 6. The participants and treating physicians will be blinded to the treatment group allocation. Patients will be randomized to one of two strategies: angiography-guided (reference) or QFR-guided revascularization (experimental). In the reference arm, any decision regarding the treatment of non-culprit lesions will be based on the angiography performed at the time of the index PCI and the physicians will be kept blinded to the outcomes of QFR analysis. This strategy reflects the typical procedures used in daily routine; all lesions believed to be significant at angiography will be treated in one staged session. In patients randomized to QFR-guided revascularization, all lesions (one or more per vessel) associated with a vessel QFR <0.80 and a residual QFR >0.80 will be treated in one staged session (13). The treatment plan will be scheduled (according to angiography or QFR) by study investigators not involved in patient care. Only experienced medical staff, certified to use the software with the QFR system, will perform the measurements. Analyses will be conducted with QAngio XA 3D from Medis Medical Imaging Systems BV (Leiden, the Netherlands).

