### Study Endpoints

*Primary endpoint (functional): the primary endpoint (functional) is* the proportion of patients assigned to medical treatment in the two groups (QFR vs. Reference) (see Table 2).

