**Table 2 T2:**
[figure not shown]
Study endpoints.

*Primary endpoint (clinical):* the primary endpoint (clinical) is a composite of patient-oriented events and significant angina (all-cause death, non-fatal myocardial infarction including type 1, 2, 4, unplanned hospitalization for angina or heart failure, unplanned revascularization, SAQ <90) at 12 months.

*Secondary endpoints:* the secondary endpoints include the following (at 3 and 12 months):

– the percentage of discordant results between functional (QFR ≤ 0.80) and angiographic coronary stenosis severity (diameter stenosis >70%).– the change in severity of angina pectoris as assessed by the SAQ summary score.– changes in the SAQ-7 domains (SAQ Physical limitation scale; SAQ angina stability scale; SAQ angina frequency scale; SAQ quality of life; SAQ Treatment Satisfaction).– incidence of a patient-oriented composite endpoint and its components (cardiovascular death, non-fatal myocardial infarction including peri-procedural, unplanned revascularization, unplanned hospitalization for angina, SAQ summary score <90) and its individual components.

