### Statistical Analysis of Primary and Secondary Endpoints

Data will be presented as counts (percentages) and mean ± SEM as appropriate and will be analyzed using parametric or non-parametric tests. The primary functional endpoint will be assessed as difference in proportions and the relative risk between groups will be estimated with exact 95% confidence intervals and *P*-values. The proportion of patients with primary functional clinical endpoint and other binary outcomes will be analyzed using the same methods, and time to events within 12 months will be compared between groups using log-rank tests. A multivariable stepwise linear regression (*p* < 0.2 to enter, *p* < 0.1 to stay) analysis will be used. Covariates will include age, sex, diabetes, smoking, renal function, previous myocardial infarction, type of acute coronary syndrome presentation, body mass index, vessel(s) involved. The grouping factor (QFR vs. angiography) will be forced into the model. A *p*-value <0.05 (2-sided) will be considered statistically significant. All secondary endpoints will be analyzed by descriptive statistics and appropriate exploratory *p*-values.

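### The QFR thresholds disagree at exactly 0.80: such a vessel goes untreated in the QFR arm but is scored significant, and a residual QFR of 0.80 is randomised but cannot be treated there

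*Protocol article*

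**What the plan says.** Under Consent and Randomization, QFR is measured in every participant before randomisation, in each artery with a 30–90% stenosis. Three rules then follow.

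- Exclusion: "Patients with vessels with residual QFR <0.80" are not enrolled. The stated reason is that "A QFR <0.80 assumes that treatment of this/these focal lesion(s) would not remove the source of ischemia".
- Randomisation comes next: "Thereafter, randomization will be performed in a 1:1 ratio".
- Treatment in the QFR arm: lesions "associated with a vessel QFR <0.80 and a residual QFR >0.80 will be treated in one staged session".

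Under Study Endpoints, one secondary endpoint is the percentage of discordant results between "functional (QFR ≤ 0.80) and angiographic coronary stenosis severity (diameter stenosis >70"%). The primary functional endpoint is "the proportion of patients assigned to medical treatment in the two groups (QFR vs. Reference"). The Discussion also uses a QFR of 0.80 or below, as the prognostic cut-off in the group's earlier study.

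**The concern.** A QFR of 0.80 is the trial's decision threshold, and the article writes it with signs that do not agree at the boundary.

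**Vessel QFR.** The treatment rule takes 0.80 as not significant; the discordance endpoint takes it as significant. For readings at that value, the endpoint would not describe the classification that decided treatment.

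**Residual QFR.** The exclusion and treatment conditions look as if they were meant to be complements, but they leave out one value. A QFR-arm patient with a vessel below 0.80 and a residual of exactly 0.80 is enrolled, and the lesion then fails the treatment condition. If there is no other treatable lesion, the patient counts as assigned to medical treatment.

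**Working it through.** The plan states no figure to reproduce here. The check applies the written rules to values on either side of the boundary.

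**Rules**
1. Exclude if residual QFR <0.80 (Consent and Randomization).
2. In the QFR arm, treat if vessel QFR <0.80 and residual QFR >0.80 (same section).
3. Score as functionally significant if QFR ≤0.80 (Study Endpoints). The endpoint says only QFR; vessel QFR is the natural reading and is assumed here.

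| Vessel QFR | Residual QFR | Enrolled? | Treated in QFR arm? | Scored significant? | Consistent? |
|---|---|---|---|---|---|
| 0.79 | 0.79 | no | – | – | – |
| 0.79 | 0.80 | yes | no | yes | no (residual gap) |
| 0.79 | 0.81 | yes | yes | yes | yes |
| 0.80 | 0.79 | no | – | – | – |
| 0.80 | 0.80 | yes | no | yes | no (vessel mismatch) |
| 0.80 | 0.81 | yes | no | yes | no (vessel mismatch) |
| 0.81 | 0.79 | no | – | – | – |
| 0.81 | 0.80 | yes | no | no | yes |
| 0.81 | 0.81 | yes | no | no | yes |

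**Residual gap.** After rule 1, all randomised patients have residual QFR ≥0.80. The part of that set failing residual >0.80 is the single value 0.80. The gap changes a treatment decision only when vessel QFR is also below 0.80.

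**Vessel mismatch.** Changing rule 3 from ≤0.80 to <0.80 flips the discordance status of each reading at 0.80:
- Stenosis of 70% or less: discordant under ≤0.80, concordant under <0.80.
- Stenosis above 70%: concordant under ≤0.80, discordant under <0.80.

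The net effect on the percentage could go either way. The effect on the primary functional endpoint is zero, because rule 3 assigns no treatment.

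**Size per patient.** The planned proportions on medical treatment are 33% (QFR) and 13% (angiography), from Power Calculation. The planned size is 100 per group, from Hypothesis.
- As planned: 33/100 vs 13/100; difference 20 percentage points; relative risk 33/13 = 2.54.
- One more QFR-arm patient on medical treatment: 34/100 vs 13/100; difference 21 points; relative risk 34/13 = 2.62.

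This shows what any one patient contributes. It says nothing about how often the gap occurs. It also needs a patient with no other lesion that qualifies for PCI, and the population section allows several: "Patients with multiple lesions and/or lesions in more than one vessel can be included".

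**The case against.** **No effect has been shown.** The article gives neither the QFR distribution nor the recording precision. If values are kept unrounded, exact 0.80 readings may be almost absent. This stands, and it limits the point to minor.

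**The endpoint need not mirror the treatment rule.** Its angiographic cut-off of 70% is not the reference arm's rule either; that arm treats whatever is judged significant on angiography. This stands in part. The endpoint can be defined independently, but using a different sign at the QFR value that drives treatment serves no stated purpose. The analysis is exploratory in any case: "All secondary endpoints will be analyzed by descriptive statistics and appropriate exploratory".

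**The article is condensed.** Its tables of criteria and endpoints are not shown, and a rounding convention may sit in the full protocol. So it cannot be said that the trial has no convention. The signs in the article's own text still differ.

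**A reader might infer that the residual treatment condition is the error, should read ≥0.80, and withholds PCI without reason.** The documents do not settle that. The explanatory sentence does cover only values below 0.80. But the discordance endpoint and the Discussion both treat 0.80 as significant. On that convention PCI leaving a residual of 0.80 leaves a significant vessel, so requiring more than 0.80 is coherent and the slip is the <0.80 in the exclusion.

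**A reader might also infer bias or loss of power.** The gap acts only in the QFR arm and towards more medical treatment, which is the expected direction. But the written QFR rule is the intervention, and assignment under it is what the endpoint measures. A power loss appears only if the vessel rule is changed to ≤0.80 and a share of patients is assumed to move to PCI. At 100 per group, power would go from 92.5% to 90.2% for a 1% shift and to 83.8% for a 3% shift. That is not the plan's rule, and neither share has a source in the documents.

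**Conclusion.** The inconsistency is real and confined to readings of exactly 0.80. For vessel QFR, treatment and the discordance endpoint classify that value in opposite ways, which affects one descriptive secondary endpoint. For residual QFR, exclusion and treatment are not complementary, and the text does not show which sign was meant. Severity is minor: the number of affected readings is unknown, the treatment rule gives a definite assignment at every value so the primary functional endpoint is unambiguous, and sample size and power are unaffected. The conclusion assumes that QFR in the discordance endpoint means vessel QFR, and that the article's inequalities are those actually applied.

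**What to change.** 1. Leave the vessel treatment rule (<0.80) as it is. Trial Status puts first enrolment in October 2020, so patients have already been assigned under it.
2. Define the discordance endpoint with the same cut-off, QFR <0.80, and show the ≤0.80 version, which is the Discussion's cut-off, as a sensitivity result.
3. For any patient not yet randomised, make the residual conditions complementary: either exclude at ≤0.80 or treat at ≥0.80, following the convention actually used. If no patients remain to be randomised, leave the rule unchanged. That may already be so, since completion was expected in May 2022.
4. List enrolled patients with a vessel or residual QFR of exactly 0.80 and how each was handled.

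The cost is one inequality in an endpoint definition, at most one in the residual rules for future patients, and a short listing from measurements taken before randomisation. No new data are needed, past assignments stand, and the sample size does not change.

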With regards to the change in SAQ, this endpoint was also used in a number of studies, including the ISCHEMIA trial (24): In the TARGET FFR study (25), 260 patients received first angiographically guided PCI and were then randomized (1:1) to a physiology-guided incremental optimization strategy or a blinded coronary physiology assessment. SAQ was a secondary endpoint in this study. A direct comparison with our protocol is impossible (all patients received PCI in TARGET FFR, while our hypothesis is that QFR will prevent futile PCIs and increase necessary ones), however the change in SAQ summary score at three months in both groups was in the range of 21 ± 25. Patients with a larger FFR change had a higher 3-months SAQ (86 ± 24 vs. 72 ± 30, *P* = 0.02 with *n* = 47 and 52 per group). If a similar difference were to be observed in our study, 144 patients would be required with a 90% 1-beta and a 5% alpha. In the FORZA study (23), the SAQ similarly improved from ~82 to ~98 (data reported only in online Figure 1). If we assume a SAQ of 98 in the QFR group and 86 in the reference group, with a SD of 21, 130 patients would be necessary.

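### The reference arm's contribution to the functional primary endpoint is an unthresholded judgement that appears to be made after allocation by planners who must know the arm, and the endpoint as defined shows only net change

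*Protocol article*

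**What the plan says.** All statements here are from the Protocol article.

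- **Endpoint.** Study Endpoints defines the functional primary endpoint as "the proportion of patients assigned to medical treatment in the two groups (QFR vs. Reference"). The treatment decision is therefore the outcome.
- **Sequence.** Consent and Randomization states: "Prior to randomization, QFR will be measured in all participants in all coronary arteries presenting a lesion with 30–90% diameter stenosis". After an exclusion based on residual QFR, it continues: "Thereafter, randomization will be performed in a 1:1 ratio with the use of randomly permuted blocks of 2, 4 or 6".
- **Who plans.** The same section states: "The treatment plan will be scheduled (according to angiography or QFR) by study investigators not involved in patient care".
- **Decision rules.** In the QFR arm the rule is numeric (vessel QFR below 0.80 with residual QFR above 0.80). In the reference arm, "all lesions believed to be significant at angiography will be treated in one staged session"; no stenosis threshold is given. Eligible lesions span roughly 30 to 90% diameter stenosis.
- **Blinding.** To allocation: "The participants and treating physicians will be blinded to the treatment group allocation". To QFR results, in the reference arm: "the physicians will be kept blinded to the outcomes of QFR analysis".
- **Hypothesis on direction.** Power Calculation, in its discussion of the SAQ, says that "our hypothesis is that QFR will prevent futile PCIs and increase necessary ones".

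**The concern.** Nobody can plan by angiography in one patient and by QFR in the next without knowing the arm. If the same people also judge the reference-arm angiogram, the outcome in that arm is a subjective call made with knowledge of allocation. The QFR arm leaves little room for judgement, so the exposure lies almost entirely on one side. Calling a borderline lesion significant in a reference patient lowers that arm's medical-treatment rate, which is the direction the trial hopes to show (33% with QFR against 13% with angiography). Blinded adjudication does not help, because the article applies it to clinical events and not to this assignment.

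The second issue is what the endpoint can express. Preventing futile PCI raises the medical-treatment proportion and adding necessary PCI lowers it. A difference in proportions reports only the balance of the two.

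**Working it through.** **1. The plan's own figure.** Inputs from Power Calculation: 33% vs 13%, 90% power, 5% level; Statistical Analysis gives two-sided testing. With unpooled variance:

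n per arm = (1.960 + 1.282)² × (0.33×0.67 + 0.13×0.87) / 0.20² = 10.51 × 0.3342 / 0.04 = 87.8, so 88 per arm and 176 in total.

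This matches the stated 176. There is no arithmetic error; the point concerns how the endpoint is generated.

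**2. Who is covered by which blinding.**

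| Role | Blinded to allocation? | Blinded to QFR result? |
|---|---|---|
| Participants | Stated | Not stated |
| Treating physicians | Stated | Stated for the reference arm, if they are the physicians meant |
| Planners | Cannot be, since they apply the arm's method | Not stated, unless they are the physicians meant |

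**3. Sensitivity of the endpoint to arm-aware judgement.** The shift sizes are assumptions; the documents give none. Take 100 per arm (the planned enrolment), a two-sided 5% two-proportion test by normal approximation, and the same true rate in both arms. Let p1 be the QFR-arm rate, p2 the shifted reference rate, d = p1 − p2 and p̄ their mean.

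se0 = √(2p̄(1−p̄)/100), se1 = √((p1(1−p1) + p2(1−p2))/100)

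P(reject) = Φ((d − 1.96·se0)/se1) + Φ((−d − 1.96·se0)/se1)

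- True rate 33%, 5 of 100 moved (33% vs 28%): se0 = 0.0651, se1 = 0.0650. P = Φ(−1.19) + Φ(−2.73) = 0.119, about 12%.
- True rate 33%, 10 of 100 moved (33% vs 23%): se0 = 0.0635, se1 = 0.0631. P = Φ(−0.39) + Φ(−3.56) = 0.349, about 35%.
- True rate 13% (the article's angiography rate), 3 or 5 of 100 moved: about 10% or 21%.

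With no shift the rate is 5% in each case.

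**4. What a net proportion leaves open.** Let a be the share moved by QFR from PCI to medical treatment and b the share moved the other way. Going from 13% to 33% fixes only a − b = 0.20. Since b can lie anywhere between 0 and 0.13, the total reclassified (a + b) can be anything from 20% (20% one way, none the other) to 46% (33% one way, 13% the other). Equal flows of 10% each way would give a net difference of zero.

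**5. What a paired table could deliver.** Assume a = 25% and b = 5%. The paired standard error is √((a + b − (a − b)²)/n) = √(0.26/n).

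- Reference arm only, n = 100: 0.051, a 95% half-width of about 10.0 points.
- All patients, n = 200: 0.036, about 7.1 points.

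**The case against.** **The article does not say that the planners judge the angiogram, or when.** It says they schedule the plan. It also ties reference-arm decisions to the index angiogram and describes them as routine practice. Clinicians unaware of the arm could make the judgement, with the planners only passing on whichever plan applies; the bias route would then largely close. This stands as a limit: planning after allocation by arm-aware assessors is a strong inference from the order of the text, not stated text. It does not dispose of the point, because nothing in the section fixes the angiographic decision before allocation.

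**Blinding to QFR results is a real safeguard.** It is, but against a different route. It does not conceal the arm, and the text leaves open whether the physicians meant are the planners.

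**The shifts are hypothetical.** This stands. Moving 10 of 33 conservative patients would overturn 30% of such decisions. The figures show how sensitive the endpoint is, not that bias has occurred; a reader who infers actual bias goes beyond the documents.

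**A net proportion answers the question asked.** The two-way statement comes from the SAQ discussion, while the functional endpoint is powered on a net difference. This is fair as to the primary test. The two-way expectation is nonetheless the article's own, and no analysis is specified to show it. The secondary discordance endpoint is a single percentage and uses a diameter stenosis above 70%, which is not the stated reference-arm rule.

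**Could one infer that the trial cannot show two-way reclassification at all?** No. QFR is measured in everyone, so each of about 100 reference patients has both an angiographic decision and a QFR result. The limit applies to the primary endpoint as defined and to the lack of a planned table.

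**Conclusion.** The point holds with moderate confidence and should be addressed. As Consent and Randomization reads, half of the functional primary comparison rests on an unthresholded judgement that appears to follow allocation and to be made by people who must know the arm, and no stated blinding clearly covers them. The endpoint is therefore open to bias in the hypothesised direction. Under assumed shifts of 5 or 10 per 100, a true rate of 33% in both arms and 100 per arm, the nominal 5% error becomes about 12% or 35%. These figures use a normal approximation, whereas the article plans exact P-values, so they are indicative only.

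The primary endpoint also reports only net change. A two-way table is possible in the reference arm (about ±10 points if 25% move one way and 5% the other) but is not planned. The sample size of 176 is unaffected. If a locked angiographic decision before randomisation is already part of the trial's procedures, saying so would settle the bias part.

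**What to change.** 1. **Patients still to be enrolled.** Have the same investigators record the angiographic treat/defer decision for each lesion on a dated, locked form, before randomisation and without the QFR result. Use that locked decision as the reference-arm plan.
2. **Supportive table.** Cross-tabulate angiographic decision by QFR decision within patients, and report both reclassification rates with a McNemar-type confidence interval. Include every patient with a locked decision, plus the reference-arm patients already enrolled, whose actual assignment supplies the angiographic decision. With all 200 patients the half-width would be about 7.1 points under the assumption above. Recruitment began in October 2020 (Trial Status), so the achievable figure lies between 7.1 and 10.0.
3. **Patients already enrolled.** Keep the assignment actually made as the endpoint. Replacing it with a retrospective reading would change the endpoint that Study Endpoints defines. A re-read of stored angiograms, blinded to arm and QFR, is an optional sensitivity analysis only.
4. **Text.** State who makes the angiographic judgement, when, and what that person knows of arm and QFR.

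The cost is one short form per patient and one extra table. The downside is that an angiographic decision is recorded but not acted on in the QFR arm. The sample size and the arms' treatment rules do not change.
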